Starting in June 2011, the counselors trained in CBI will begin to implement this intervention with the clients that come to see them as part of the ongoing services provided by AAPP, SAW, and MTC. A practicum round of the CBI intervention began shortly following the CBI training in order to be sure that counselors and supervisors are properly trained in the intervention. The research study will begin in June 2011 when approximately 400 people will be screened into the intervention (for a final sample of 300); approximately half of these would be randomly assigned to the “case” group, to begin the intervention immediately after screening while the other half would be assigned to the “wait-control” group to receive CBI after the “case” group has completed the CBI intervention.

The proposed study will be embedded within the ongoing MTC, SAW and AAPP programs which could include non-specific counseling services, social services and support and, in the case of Mae Tao clinic, medical assistance. That is, we are proposing to study the effectiveness of these intervention strategies in a subset of the clients the organizations serve. The organizations will continue to provide services, as space allows, to anyone who seeks their services regardless of whether they meet eligibility for our proposed study. However, those who meet our inclusion criteria will be invited to participate in the research component of the service program.

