### **3. Participants:**

Persons eligible for participation in this study will include the following: adults from Burma (18 and older) living in Mae Sot with significant mental health problems; who were affected by torture and systematic violence (that is either directly subjected to torture and imprisonment, or indirectly

through witnessing torture, or who are a close family member of a survivor) and who are not actively suicidal. Eligible persons will mainly be located with the assistance of our local organizational counterparts. Some may be former prisoners who were tortured in prison by the Burmese military regime. Others will be identified as they present to the local organizations seeking help for various problems, including mental or physical disorders. All those who are found to be eligible will be invited to join the trial.

Screening will be done using an instrument developed for use among this population (see attached document). For the baseline interview, Section 1 (Demographic Characteristics), Section 2 (Trauma Events), Section 3 (Depression Symptoms) and Section 4 (Trauma Symptoms) will serve as the screening tool to identify persons found to have experienced or witnessed torture or systematic violence and who exhibit significant symptoms of trauma or depression. This will comprise Part A: Screening Instrument of the baseline interview.

Those who are found to be eligible on exposure and symptoms criteria—and who are also eligible by being adults from Burma living in Mae Sot, Thailand—will be consented to continue the full intake/assessment interview and to join the trial. Part B of instrument comprises the intake/assessment portion, and includes Section 5 (Anxiety), Section 6 (Function Assessment), Section 7 (Current Problems), Section 8 (Aggressive Behavior) and Section 9 (Alcohol Use).

There may be some individuals who are deemed eligible and have consented to participate in the study but who, following the full intake interview, would be deemed excludable either because they are a danger to themselves or others, or who are psychotic or otherwise deemed not competent to give consent or participate in the interventions. While we believe the study intervention is not appropriate for these individuals, counselors will review the cases with their clinical supervisors and the JHU study team to ensure that every effort is made to provide these individuals with referral to appropriate care.

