##### *2) Study procedures, including their sequence and timing.*

*Recruitment:* Beginning in May 2011, recruitment for the intervention effectiveness study will begin. Recruitment of persons for screening and enrollment will be done by contacting the local organizations and inviting program beneficiaries and community members to come to the counselors to be screened. Recruitment will be done by word-of-mouth and through routine program contacts with the community. Local partner organizations (BBP, AAPP, MTC and SAW) have developed a one-page handout and pamphlet in the local language (Burmese) that provides a brief description of the project and contact information for persons in the project whom they can contact for more information. These contact persons with the local partner

organizations will then collect names and contact information for those who express interest in possibly taking part in the study. The recruitment process will identify the availability of a new intervention for people who have experienced or witnessed torture or systematic violence and who feel they might benefit from counseling for depression or trauma symptoms. Potential participants will be told that the program is available for Burmese persons 18 years or older who will remain in the Mae Sot area for the duration of the intervention (10 weekly sessions). Persons expressing an interest in being contacted for a follow-up discussion will be invited to provide their contact information to the local program staff-members as mentioned above. We anticipate that the recruitment process will take approximately 4-8 weeks, to be carried out as counselors and clinical supervisors are completing a practicum period of training in the CBI method (March – June 2011). All contact information will be collected from the local partner organizations by the on-site JHU Project Director who will maintain the overall file of potential clients for the study. Local partner organizations will be asked to destroy their copies of the names and contact information as this will be maintained only by the Project Director on a secure file.

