*Training on Consent and Screening Procedures:* We plan to begin the actual intervention study with CBI in June 2011 (corresponding to Month 5 in the table below). Prior to that, JHU study faculty will provide training to all counselors and clinical supervisors on how to carry out consent and screening procedures, including administering the study consent form and interpreting depression and trauma severity scores.

*Screening:* A screening process, and allocation to either an intervention (case) group or temporarily to a wait-control group, will continue until the practicum round of CBI training has been completed in late June or early July. If a sufficient number of clients for the intervention group are not identified by early July, screening and enrollment could continue beyond that time.

*Service Provision:* Beginning in late June or early July 2011, the intervention will begin with weekly sessions provided by the counselors to the client and with supervision provided in the form of weekly meetings between the counselor and clinical supervisor and in the form of weekly phone conversations between the clinical supervisors and the JHU trainers/clinical psychologists. Both intervention and control clients will be monitored using separate client monitoring forms. These forms will include information on the clients' well-being, any treatment or medication they are receiving, and whether or not the client's are in danger to themselves or others. Clients who are in danger of committing suicide will be discussed immediately with supervisors, or referred if supervisors are not immediately available. There is a Safety Plan (see attachment) in place for this project that includes a response team of the following: the counselor, the counselor's clinical supervisor, a medical doctor who is part of the project team, and the Field Project Coordinator. The Project Director will provide support for this response team at all times and will be in regular contact with the Project PI. A copy of the Safety Plan protocol is included in the IRB application.

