Persons who are in the intervention group or the wait control group whose depressive symptoms worsen (but not to the point of ineligibility) would first be evaluated by the counselor in conjunction with the study's clinical team and with the CCT medical monitor. Based on this assessment, a decision could be made to continue CBI treatment alone or the client could be provided referral to standard of care treatment possibly including non-specific counseling. This treatment would be recorded in the client monitoring records.

We should note that some of the counselors who will deliver the CBI intervention are also qualified to provide other services (for example, some of the Mae Tao Clinic counselors providing the intervention also work at the Counseling Center on a part-time basis). We will ask for the period of the intervention, that the CBI counselors provide only CBI to their study clients. If referrals are made for other services (or clients independently seek other services including,

possibly, non specific counseling) these other services would be provided by someone other than the CBI counselor.

|                                                               | Month |    |    |    |    |    |    |    |    |    |    |    |
|---------------------------------------------------------------|-------|----|----|----|----|----|----|----|----|----|----|----|
|                                                               | 1     | 2  | 3  | 4  | 5  | 6  | 7  | 8  | 9  | 10 | 11 | 12 |
| 1. Training on CBI Method                                     | XX    | XX |    |    |    |    |    |    |    |    |    |    |
| 2. Practicum Round on CBI                                     |       |    | XX | XX | XX |    |    |    |    |    |    |    |
| 3. Recruitment                                                |       |    |    | XX | XX |    |    |    |    |    |    |    |
| 4. Screening and Baseline Interviews of Case and Wait-Control |       |    |    |    | XX | XX |    |    |    |    |    |    |
| 5. Intervention (Case Group)                                  |       |    |    |    |    | XX | XX | XX | XX | XX |    |    |
| 6. Follow-up Interviews (Case and Wait-Control Groups)        |       |    |    |    |    |    |    |    |    | XX |    |    |
| 7. Intervention for Wait-Control Group                        |       |    |    |    |    |    |    |    |    | XX | XX | XX |

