All adults who meet with one of the 20 trained counselors will be verbally consented and screened by the counselors for study eligibility. Counselors will first re-confirm that the person lives in Mae Sot, will be available for the duration of the study, and is 18 years or older. The screening interview will then be used to establish whether the individual meets our definition of exposure to torture or systematic violence (experienced or witnessed at least one trauma exposure event), and has significant depression and/or trauma symptoms (as noted previously, the scores are 13 or above for depression symptoms and 45 or above for trauma symptoms).

Exposure to torture and violence will be measured through a review of the trauma exposure questions on the assessment interview. There are 25 questions that ask about exposure to traumatic events. If the respondent indicates that they personally experienced or witnessed any of these for exposures, they will be regarded as having been exposed to torture for purposes of this study. If they are not eligible for our study, they can continue to receive counseling and support as per existing standards of care and service provided by the local participating organizations.

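### Trial screening overlaps a practicum round of CBI run by the same counselors, and no eligibility criterion addresses earlier CBI, so the CBI versus no-CBI contrast may be diluted

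*Protocol*

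**What the plan says.** **The practicum.** Section 2 reports that "A practicum round of the CBI intervention began shortly following the CBI training in order to be sure that counselors and supervisors are properly trained". The training was held in February-March 2011. Under Recruitment in Section 4, item 2, recruitment is "to be carried out as counselors and clinical supervisors are completing a practicum period of training in the CBI method (March – June 2011").

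**The overlap.** The Screening paragraph of the same item says that screening and allocation "will continue until the practicum round of CBI training has been completed in late June or early July". The timetable there places the row "2. Practicum Round on CBI" in Months 3-5, recruitment in Months 4-5, and the row "4. Screening and Baseline Interviews of Case and Wait-Control" in Months 5-6. June 2011 is given as Month 5.

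**Who is approached.** Recruitment draws on program beneficiaries and routine program contacts (Section 4, item 2). It also draws on people whom counselors see in their normal work (Section 6a). Section 4, item 7 then states: "All adults who meet with one of the 20 trained counselors will be verbally consented and screened by the counselors for study eligibility". Section 3 adds: "All those who are found to be eligible will be invited to join the trial".

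**Who qualifies.** The criteria in Section 3, Section 4 item 7 and Section 7a are:
- adult age, origin in Burma, residence in Mae Sot and availability for the study;
- at least one trauma exposure;
- a depression score of 13 or more and/or a trauma score of 45 or more;
- not actively suicidal, dangerous, psychotic or incompetent to consent.

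None concerns earlier CBI. The stated comparison, in Sections 1 and 4 item 9, is CBI against no CBI.

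**The concern.** A trial of CBI against no CBI needs control participants who have not had CBI. Here the staff who screen are the staff who have been practising the intervention, they recruit from their own contacts, and the two activities run side by side for part of the screening period. Nothing in the eligibility rules separates people already treated in the practicum from people who have never been treated.

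If such people enter, two things follow. A wait-control participant may have had some or all of the intervention shortly before baseline. A case participant may have a baseline taken after part of the benefit has occurred, and then repeat components already covered. Section 4, item 5 attributes the whole difference in mean change to the intervention and analyses everyone enrolled by intention to treat, so these participants would count fully. Eligibility is settled in the protocol, so a later analysis plan cannot restore the intended comparison. Nor could it rely on a baseline record of earlier CBI, because none of the instrument sections listed in Section 3 names one.

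**Working it through.** **1. Timing.** Practicum: Months 3, 4, 5. Recruitment: Months 4, 5. Screening and baseline: Months 5, 6. Practicum and recruitment share Months 4 and 5. Practicum and screening share Month 5. The Screening paragraph agrees, since it ties the end of screening to the end of the practicum.

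**2. Whether the practicum involves clients.** No sentence says so.
- For: Section 2 calls it a round of the intervention itself. The role-plays were already part of the 10 training days, and the practicum is separate and lasts about three months. Section 4, item 1 says the counselors were trained to give CBI to all survivors they treat.
- Against: Section 2 also says counselors will begin using CBI with their clients starting in June 2011. Section 4, item 2 describes the practicum as training.

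Real clients are therefore the more natural reading, but an inference.

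**3. Whether such a client could be randomised.** A practicum client who has fallen below both cutoffs is screened out. One who is still at or above either cutoff meets every listed criterion and can go to either arm.

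**4. The plan's own sample size.** Inputs from Section 4, item 14: effect 0.50 SD, power 0.80, alpha 0.05 (taken as two-sided), design effect 1.5, drop-out 25%, 1:1 allocation.
- Two-sample t-test: 63.8, so 64 per arm.
- 64 × 1.5 = 96.
- 96 × 1.25 = 120 per arm, the stated figure.
- Dividing by 0.75 instead gives 96 / 0.75 = 128, which the recruitment target of 150 per arm covers.

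Effective size at that target: 150 × 0.75 / 1.5 = 75 per arm.

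**5. Illustration of dilution.** The number of practicum clients is not given. Let a share f of participants, equal in both arms, have had CBI, and let them keep a fraction k of the planned between-arm effect. The average effect is then d = 0.50 × [1 − f(1 − k)]. Assumed for scale only: 1, 2 or 3 such people per counselor, that is 20, 40 or 60 of 300. Power is for a two-sided t-test with 75 per arm.

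| Share f | d, k = 0 | Power, k = 0 | d, k = 0.5 | Power, k = 0.5 |
|---|---|---|---|---|
| 0 | 0.500 | 0.86 | 0.500 | 0.86 |
| 20/300 = 7% | 0.467 | 0.81 | 0.483 | 0.84 |
| 40/300 = 13% | 0.433 | 0.75 | 0.467 | 0.81 |
| 60/300 = 20% | 0.400 | 0.68 | 0.450 | 0.78 |

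Power reaches the planned 0.80 at a share of about 8% if no effect remains (k = 0), and at about 16% if half remains (k = 0.5).

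**The case against.** The strongest objection is that treated practicum clients are not documented, neither their existence nor their number. This stands. The concern is conditional, and one sentence saying that no clients received CBI in the practicum would close it.

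Second, entry is not automatic. A practicum client would have to come forward, consent, and accept a possible wait of 3 to 4 months for something offered as a new intervention. This also stands: the plan permits such enrolment but does not make it happen.

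Third, a reader might infer that the trial is biased, with treated people collecting in the control arm. The documents do not support that. Allocation is random and 1:1, so earlier exposure is balanced on average, and baseline follows that exposure in both arms alike. Nor do they support the idea that wait-controls would carry on with practicum sessions, since Section 4, item 10 says controls do not initially receive treatment. Continuing would be a departure from the protocol.

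Fourth, the power figures rest on assumptions without a source. With roughly 15 ID numbers per counselor, three returning clients would be one in five of the list, and no further between-arm effect is a harsh assumption when case participants would receive about 10 more sessions and controls none. At the low end power stays above 0.80 even so. This stands against reading the table as an estimate.

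Finally, the screening instrument is an attachment that is not shown, and it may ask about earlier treatment. Even so, no stated criterion would act on the answer.

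**Conclusion.** The point holds as a gap in the eligibility rules. The overlap in time, the shared counselors, the recruitment from program contacts and the absence of any criterion on earlier CBI are all on the page. Followed as written, the plan allows recently treated or part-treated people to be randomised, including to an arm meant to represent no CBI.

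The conclusion depends on the practicum having treated real clients, some of whom remain at or above a cutoff and enrol. On that condition the expected consequence is an effect estimate pulled towards zero and some loss of power. The size is unknown. The range of 0.81 to 0.68 for shares of 7% to 20% applies only if no between-arm effect remains in these people.

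A reader might also infer that those who re-enter are simply CBI non-responders. That could describe people who finished the practicum and still qualify, but those midway through are better described as part-treated, and the protocol does not distinguish the two. The gap merits correction because it touches the stated comparison and is inexpensive to close.

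**What to change.** Add to the eligibility text in Section 3 and in Section 4, item 7 that anyone who has received any CBI session, including in the practicum, is not eligible for randomisation. Add a question on earlier CBI to the screening interview, so that the criterion is checked and the answer recorded. No practicum client list is described in the protocol, so the check should not depend on one.

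No design input changes and the sample size stays as it is. The cost is one criterion, one question and a small number of candidates lost from the roughly 400 to be screened. Section 4, item 7 already says what happens to people found ineligible, and this change does not alter that.

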Measures of trauma or depression symptoms will be based on the responses to all trauma and depression questions in the screening interview. The counselors will calculate the total score for these questions (defined as the total trauma and depression subscales) while the interviewee is still present. If this meets or exceeds a cutoff score of 45 for trauma---reflecting likely clinically significant symptoms (based on results of a previous validity study of the instrument among the same population) and/or a cutoff score for depression of 13 or more ---reflecting likely clinical significant depression (again based on results of the previous validity study)---then the person will be invited to join the trial after having been read a consent form which explains the trial. If they agree they will be assigned either to receive treatment beginning soon or be told that they are on a wait-list and will need to wait several months before receiving treatment. If they are eligible but decline to participate in the trial, the counselor and clinical supervisor, in consultation with the JHU study team, will review treatment options on a case-by-case basis. Depending on the outcome of this assessment, these individuals could be offered to receive the study treatment (though not participate in the study) or they could be referred to other appropriate programs and services in the Mae Sot area.

While the study imposes no upper cut-off point for depression and trauma symptoms (and thus would not exclude persons with acute mental illness), there may be some individuals who are deemed eligible and have consented to participate in the study but who would be excludable either because they are a danger to themselves or others, or who are psychotic or otherwise deemed not competent to give consent or participate in the interventions. While we believe the study intervention is not appropriate for these individuals, counselors will review the cases with their clinical supervisors and the JHU study team to ensure that every effort is made to provide these individuals with referral to appropriate care.

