In the case of individuals who evidence signs of active suicidal ideation, counselors and clinical supervisors have been trained on suicide assessment as part of their CBI training. In all cases involving potential danger of a client harming him/herself or others, counselors will follow the study Safety Plan to request assistance in assessing the need of follow-up care and services for that individual. On a case-by-case basis, the study team will work with the counselor and clinical supervisor, along with [name] and the study team's clinical experts, to determine whether to offer the individual the study treatment (if they are excludable from the study intervention), or the study intervention (if they are otherwise eligible and no longer deemed an active risk to harm themselves or others), or some other available and appropriate treatment.

*Randomization process:*

If the subject is deemed eligible and consents to join the trial, the subject will be randomly allocated to the case group to receive treatment immediately or to the wait-control group. The randomization process will be as follows:

1. Each counselor will receive a list of participant ID numbers in sequence (i.e. 1-15) which have been randomly allocated to either intervention or wait-control via a random number generator, with a 1 to 1 ratio of intervention to wait-list. There will be one list for each counselor. Counselors will not be aware how numbers have been allocated.
2. For each counselor, a paper indicating the treatment assignment (intervention or wait-list) will be folded and stapled directly to the back of consent forms that are pre-numbered with a client ID number.
3. Once the subject has consented to be in the study, the counselor will assign a number to the client in the order in which they are recruited. They will remove and unfold the paper attached to the form that corresponds to their ID number, and will inform the subject whether they will begin the intervention immediately or will be put on the wait list.

The study investigators will keep master lists for each counselor which indicate the allocated group status (intervention or wait-control) for each client ID number to ensure fidelity to the randomization model.

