## **7. Consent process and documentation:**

- a. *Describe who will obtain informed consent from participants, and how, when and where consent will be obtained.*

Prior to the screening process and intake interview, the counselor will verbally consent participants, informing them of the interview process, the intervention therapy, the re-interview process and the possible risks and benefits of participation. The interview will take place at a private location convenient to the potential client and could include the BBP, AAPP, SAW, or MTC offices or a private home. At the beginning of the consent process, the counselor will establish that the person meets eligibility criteria for inclusions—that is, they are 18 years or older, a Burmese national, and resident in the Mae Sot area. During the oral consent process, the potential client will be informed that they will first be asked a series of screening questions to assess their mental health symptomology. If the person is determined to be eligible for inclusion in the intervention study on the basis of these higher symptom scores, they will be told that they will be randomized into a case group or wait-control group and informed that they will either start the intervention within approximately one week or will be asked to wait several months. Following the intervention, both groups will be re-interviewed.

Thus the screening consent form will offer a recruited individual to consent to be screened for trauma exposure and for depression and trauma symptoms only. If the individual is deemed eligible for inclusion, the study consent form will offer the potential client an opportunity to complete the intake/assessment interview and to be randomized into a case or wait-control group for treatment (for the case group), and a follow-up interview several months later. For those in the wait-control group, they will be further asked if they are willing to be contacted once a month by the counselor while they are waiting for the follow-up interview.

Failure to show up for first session will disenroll a person from the study; we do not regard a client as fully consented unless they show up for Session 1 as they may have changed their mind after discussing participation with family members. If a client clearly (in the view of the counselor, clinical supervisor and study team) does not have mental capacity to give consent, then that person would not be asked to be in the study.

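### Allocation is opened at study consent, and nothing holds it back until the Part B baseline and the post-consent exclusion review are done

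*Protocol*

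**What the plan says.** **Screening and consent.** Part A (demographics, trauma events, depression, trauma symptoms) is the screening instrument (section 3). The counselor scores it with the client present: "The counselors will calculate the total score for these questions" (section 4, item 7). Clients who reach a cutoff are invited to join and are read the study consent.

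**Allocation.** Item 7 ties assignment to agreement: "If they agree they will be assigned either to receive treatment beginning soon or be told that they are on a wait-list". The Randomization process repeats this: "Once the subject has consented to be in the study, the counselor will assign a number to the client". The counselor then opens the assignment ("They will remove and unfold the paper attached to the form that corresponds to their ID number") and tells the client the result.

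**Part B and exclusion.** Under section 3, eligible clients consent both to the full intake interview and to joining the trial. Some people who are already eligible and consented may still be found unsuitable: "but who, following the full intake interview, would be deemed excludable either because they are a danger to themselves or others". Psychosis and lack of competence are the other grounds. Counselors review these cases with their clinical supervisors and the university study team.

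**The consent section.** Section 7a says that "the study consent form will offer the potential client an opportunity to complete the intake/assessment interview and to be randomized".

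**Concealment.** The assignment paper "will be folded and stapled directly to the back of consent forms that are pre-numbered with a client ID number". The stated intent is that "Counselors will not be aware how numbers have been allocated". The investigators keep master lists linking ID to arm.

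**Analysis.** Section 4, item 5 compares mean pre-post change on the various subscales between arms. It includes, by intent to treat, those who meet the screening criteria and enroll.

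**The concern.** Randomization protects a comparison only if the decisions about who is in it, and the baseline measurements, are made without knowledge of the arm. Here the only stated trigger for opening the paper is consent, and two later steps still depend on judgement.

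- **Exclusion.** Judging risk of harm, psychosis or competence is not mechanical. If the arm is known, a borderline client could be handled differently according to whether treatment starts at once or after a wait of three to four months. Exclusions could then differ in number or kind between arms.
- **Part B baselines.** The counselor asking about anxiety, function, problems, aggression and alcohol would know the arm, and so would the client. Where these scales are analysed as pre-post change, the baseline enters the effect estimate directly. Section 4, item 8 guards the follow-up interview of case clients against counselor bias. Nothing comparable is stated for Part B at baseline.

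Neither problem can be repaired once clients have been enrolled this way.

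**Working it through.** No figure in the protocol is in dispute, so the check is of sequence.

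**Step 1: when the paper is opened.** Section 4, item 7 says in two places that assignment follows agreement to join. ID assignment, opening and disclosure form one numbered step.

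**Step 2: where Part B sits.** Section 3 puts it after study consent, because that consent covers continuing to the full intake interview.

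**Step 3: where the exclusion review sits.** Section 3 puts it after the full intake interview. Item 7 repeats the exclusion for people who have already consented.

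**Step 4: whether anything delays opening.** There are two candidates.
- The sentence introducing the randomization steps requires eligibility as well as consent. But section 3 calls people eligible before the intake interview and then describes some of them as excludable, so eligibility does not include the exclusion review.
- Section 7a names intake before randomization, but within a description of what the consent form offers. It does not make one step a condition of the other.

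No section tells the counselor to wait. Steps 1 to 3 together permit consent, opening, Part B, exclusion.

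**Step 5: what is exposed.**

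| Item | Collected or decided | Arm can be known? |
|---|---|---|
| Depression and trauma baselines | Part A, before study consent | No, if the paper is unopened |
| Anxiety, function, problems, aggression, alcohol baselines | Part B, after consent | Yes |
| Exclusion for harm, psychosis, competence | After Part B | Yes |

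**Step 6: size.** The planned estimate is a difference in mean change. Suppose a fraction q of one arm only is removed, and their mean change differs from that arm's mean change by D. The mean change of those remaining shifts by

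shift = q / (1 − q) × D.

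If D = 0 the shift is 0, however severe the excluded people were at baseline. The protocol gives neither q nor D. On purely assumed values, q from 2% to 10% (3 to 15 of 150) and D from 0.5 to 1.0 SD of change:

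- low end: 0.02 / 0.98 × 0.5 = 0.01 SD
- high end: 0.10 / 0.90 × 1.0 = 0.11 SD

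This shows how the mechanism works. It is not an estimate for this trial.

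**The case against.** The strongest reply is that the adverse order is inferred. No single sentence says that the paper is opened before Part B, and section 7a lists intake, randomization, treatment and follow-up in what looks like time order. This stands in part: a reader might infer that the protocol states the adverse order, and it does not. But the operational steps in item 7 are what a counselor would follow, and they permit it. The sections need reconciling on either reading.

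Other parts of the reply also stand:

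- **Main outcomes.** Depression and trauma, on which the sample size rests, have baselines taken before the paper is opened. A reader might infer that all baselines are compromised, but only Part B is exposed.
- **Shared decisions.** Exclusions are reviewed with supervisors and the study team, so they are not the counselor's alone. Section 7a also keeps clients who clearly lack capacity from being asked to join. These are real checks, but nothing says that the reviewers are unaware of the arm.
- **Intent to treat.** A reader might infer that exclusion after allocation contradicts the analysis commitment. The protocol does not say that people excluded after consent leave the analysis. It is silent, which is a gap and not a contradiction.
- **Concealment.** A reader might infer that counselors can or will read the assignments early. The protocol states the opposite intent, uses IDs in order of recruitment, and has separate screening and study consents. Early reading is a risk, not a documented event.

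**Conclusion.** The point holds as a defect of sequence. As written, the protocol permits post-consent exclusions and Part B baselines with the arm known, and section 7a does not settle the order the other way. The depression and trauma baselines are not affected, but selective exclusion could still alter who is compared on those outcomes.

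The conclusion rests on reading consent in section 4, item 7 as the same study consent that precedes Part B in section 3. Section 3 supports this by joining the two in one consent.

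The size of any bias cannot be derived from the documents. It is tempting to turn an assumed share of excluded, more severe clients into a percentage of the planned 0.50 effect. That does not follow, because the analysis compares change: removing severe clients biases it only if their change differs from that of the rest of their arm.

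Concealment is a secondary matter. A folded sheet stapled to the counselor's own consent forms is a weak barrier. The master list can confirm that ID and arm match, but not that the paper was unread beforehand.

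**What to change.** **Main change.** Reconcile section 3, section 4 item 7 and section 7a so that they give one order:

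1. Part A screening and scoring
2. Study consent
3. Part B interview
4. Exclusion review completed and recorded
5. ID assigned, paper opened, client told the arm

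State in section 4, item 5 that everyone allocated stays in the intent-to-treat analysis, including anyone later found unsuitable for the intervention. The rule in section 7a that disenrolls clients who miss the first session is a further removal after allocation and should be reconciled with that statement.

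**Optional second step.** Have existing staff other than the screening counselor, such as a clinical supervisor or the Field Project Coordinator, hold the assignments, or use sealed opaque envelopes. Log ID, date and eligibility before opening.

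**Cost.** The main change is protocol wording, with no change in sample size. The client learns the arm slightly later, at the end of the visit or once the review is complete. The second step adds a log entry and, if staff hold the list, one phone call per participant.
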